### Experimental intervention

SCOOT is a community-based, client-centered intervention that embeds skills training into social activities that users want to accomplish. It also uses trainer-facilitated problem solving to identify strategies to manage environmental barriers and to enable better user social participation. This intervention represents a departure from customary scooter training that is often very limited and which focuses on learning discrete skills outside of the user’s normal environment. With SCOOT, skill training (i.e., on driving, basic and advanced scooter skills) will take place during self-selected, home- or community-based activities that participants want to perform using their scooters. We will identify these activities using the WhOM [21], which identifies the most important home- and community-based activities participants wish to perform using their scooters (described below). The skills training component of the intervention is based on the scooter version of the Wheelchair Skills Training program [20].

The intervention will be held in the neighborhood of the participants, located in the Greater Vancouver Regions District of British Columbia, Canada. The intention of conducting the study within the neighborhood of the participant is to facilitate the transferability of training and to improve the ecological validity. In addition, training in the community aims to reduce participant burden of travelling to our research site, and to improve adherence. These neighborhoods are all located within an urban setting, and locations include, but are not limited to, community centers, grocery stores, and parks.

SCOOT for scooter mobility skills will be provided by occupational therapist trainers who will be trained by the principal investigator to use the same standardized approach. The therapist will keep a record of the skills that they have taught and hours of training provided. During training sessions, the therapist delivering the intervention will record any adverse effects of the intervention such as falls. We will collect data on the number of therapist visits, length of visits, therapist years of practice, years of experience working in this area, and therapist qualifications.

### Outcome measures

#### Primary outcome measure (subjective skill capacity)

The subjective version of Kirby et al.’s Wheelchair Skills Test [20] for scooters incorporates three domains of skills training, namely skill capacity, confidence, and performance. For this study, the primary outcome measure will be perceived capacity. It consists of 29 items that are scored by the participant from 0 to 2, where 0 = unsafe or unable, 1 = safe with difficulty, and 2 = safe without difficulty; a percent score is calculated by dividing the total score by the number of applicable items and multiplying that number by 100. The measure assesses basic indoor mobility skills (driving forward and backwards), transfers on and off the scooter, and outdoor driving skills, including maneuvering, curbs, and ramps. The intraclass correlation coefficient (ICC) for 2-week test-retest reliability of the Wheelchair Skills Test among power wheelchair users is 0.78 (95% confidence interval, 0.68–0.86) [25]. As scooters and power wheelchairs are both motorized mobility devices, a similar reliability among scooter users is expected.

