### Participants

For this feasibility study we plan to recruit 40 participants. As the majority of wheeled mobility users are older adults [4], the eligible community dwelling participants for this study are (1) English-speaking adults, (2) aged ≥ 60 years, (3) have one month or less combined experience of using a scooter within the past year, and (4) are able to independently transfer in and out of a scooter. We have not defined the population of interest based on their diagnoses (e.g., stroke, spinal cord injury, Parkinson’s disease), because the use of a scooter is not diagnosis specific. Individuals who have cognitive impairments that will prevent them from providing consent and from reliably completing the study questionnaires, reside in a nursing home, or plan to move outside the study intervention delivery area within the next year will be excluded.

Participants will be recruited through a variety of sources, including community healthcare units, vendors, and various seniors’ groups and seniors’ centres. Participants will be recruited through these organizations via posters, presentations, social media, and referrals. Occupational therapy staff and vendors will invite eligible clients to consider the trial.

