### Analysis

#### Quantitative data

Data will be input into a password protected document and will be double checked for accuracy. Descriptive statistics (e.g., means, frequencies, proportions, standard deviations) and distributions and box plots will be used to display all study data. The percentage of skills taught will be calculated to determine the treatment fidelity, and the percentage of sessions attended will be calculated to determine adherence. These quantitative data will be supplemented with data from the qualitative portion of the study. We will explore the use of multiple imputation for missing outcome measure data [47]. A detailed statistical analysis plan to handle various statistical analysis issues will be created [48]. To identify covariates that will be controlled for in the larger study, we will identify factors that are strongly related to the primary and secondary outcome measures. To determine the effect size for the primary and non-count secondary outcome measures, we will perform various models, controlling for baseline scores, using an intention-to-treat analysis. That is, all participants will be included in the group to which they were allocated for purposes of analysis, whether or not they completed the intervention for that group. As this is a feasibility study, we will also calculate effect sizes based on the intervention received (e.g., on an as-treated basis). Using G*Power 3.1.0, this sample size should give us the ability to detect a large effect size of 0.46 (with α = 0.05 and power = 80%). For count data (e.g., use, accidents, and falls), we will determine the effect size by using Poisson regression [49].

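### The primary outcome's percent score divides by the number of applicable items although each item scores up to 2, so as written it runs from 0 to 200

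*Protocol article*

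**What the plan says.** Everything needed stands in one paragraph of the protocol article, under Primary outcome measure (subjective skill capacity).

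- Role of the measure: "For this study, the primary outcome measure will be perceived capacity".
- Size and scale: "It consists of 29 items that are scored by the participant from 0 to 2".
- Meaning of the item scores: "0 = unsafe or unable, 1 = safe with difficulty, and 2 = safe without difficulty".
- Scoring rule: "a percent score is calculated by dividing the total score by the number of applicable items and multiplying that number by 100".

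The paragraph gives no lowest or highest value for the resulting score. The section on objective scooter skills describes a 29-item rater-administered version but gives no scoring rule, so it neither confirms nor corrects this one. No other section of the article returns to the calculation.

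**The concern.** A percent score is normally the share of the attainable points, with 100 as the ceiling. The attainable points here are 2 per applicable item, but the stated denominator counts each applicable item once. What the rule yields is the mean item score multiplied by 100, and that is not a percentage of anything.

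This sentence defines the trial's main variable. The Background section lists estimates of the intervention's effect and of its variance among the aims, and the Abstract says that the results will inform a larger trial. A reader of a raw mean or standard deviation needs to know whether the scale ends at 100 or at 200. The worst case for interpretation is a score of 100. It looks like full capacity, but under the written rule it can describe someone who reports difficulty with every skill.

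**Working it through.** **Inputs**, all from the primary outcome paragraph: 29 items; item scores 0, 1 or 2; k = number of applicable items; T = total score. The article states no range for the score, so there is no figure of its own to reproduce.

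**Rule as written:** S = T / k × 100.

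**Share of the attainable points:** P = T / (2k) × 100.

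| Case | T | k | S (as written) | P (share of maximum) |
|---|---|---|---|---|
| Every item 0 | 0 | 29 | 0/29 × 100 = 0 | 0/58 × 100 = 0 |
| Every item 1 | 29 | 29 | 29/29 × 100 = 100 | 29/58 × 100 = 50 |
| Every item 2 | 58 | 29 | 58/29 × 100 = 200 | 58/58 × 100 = 100 |
| Every item 2, 20 applicable | 40 | 20 | 40/20 × 100 = 200 | 40/40 × 100 = 100 |
| Every item 2, 10 applicable | 20 | 10 | 20/10 × 100 = 200 | 20/20 × 100 = 100 |

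The ceiling is 200 whatever the number of applicable items, and S = 2P for every participant.

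**What doubles.** Means, standard deviations, mean differences and confidence limits are all multiplied by 2. Variances are multiplied by 2² = 4. As an illustration with an assumed gain of 10 points in total score and all 29 items applicable, the change is 10/29 × 100 = 34.5 as written and 10/58 × 100 = 17.2 on the 0–100 scale.

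**What does not change.**

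- Standardised effect: (2 × difference) / (2 × SD) = difference / SD. Test statistics and p-values are likewise unchanged.
- ICC: this is a ratio of variances. Both are multiplied by 4, which cancels.
- Stated power: the Quantitative data section gives a detectable effect of 0.46 at α = 0.05 and 80% power, for the 40 participants in the Participants section. Read as Cohen's f for two groups, the noncentrality is f²N = 0.46² × 40 = 8.46. The recomputed power is 0.81, and the effect detectable at 80% power is f ≈ 0.455. This calculation contains no raw units, so the scoring scale does not enter it.

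**A later trial's sample size.** n is proportional to (SD / difference)². If both come from this study, (2 × SD / 2 × difference)² equals (SD / difference)² and n is unchanged. Only a doubled SD set against a target difference on the 0–100 scale would alter n, by 2² = 4.

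**The case against.** The strongest reply is that this is a slip in the article's wording with no effect on the data. The measure is an existing instrument cited to a source, rater training under Procedure includes the manuals and practice in scoring, and the label of percent points to an intended 0–100 scale. Even if the rule were followed literally, the factor of 2 is the same for everyone and leaves tests, standardised effects and power alone. Any participant with a mean item score above 1 would also get more than 100%. The planned double-checking of data, descriptive statistics and box plots should expose that.

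Most of this stands. The article does not show that anyone scores by the published formula, so every effect on data has to be stated as conditional. The visibility argument is sound but incomplete: a participant with a mean item score of 1 or less gets a value of 100 or below, which looks ordinary. None of it makes the sentence right. The article chose to state the formula, and that formula contradicts its own label and item scale. This is therefore not a detail left to a fuller document.

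A reader might infer more than the document supports:

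- *That the larger trial would be four times too large.* This needs literal use of the formula, no one noticing values above 100, and a target difference taken from a different scale. The article gives no raw SD, no raw target difference and no sample size method for the larger trial.
- *That the error distorts comparison with published percent scores.* The article reports no such score for this measure and plans no such comparison.
- *That baseline data have already been scored wrongly.* The trial is recruiting, but nothing says which formula has been applied.

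**Conclusion.** The scoring rule for the primary outcome is wrong as written: the score runs from 0 to 200, and difficulty on every item scores 100 where the share of attainable points is 50. The arithmetic uses only figures in one paragraph and is certain.

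The consequence is limited and conditional. On the assumption that the published formula is the one used, raw results on the primary outcome are exactly double their 0–100 values. No hypothesis test, standardised effect, reliability coefficient, power figure or feasibility threshold changes. A later sample size is affected only if the two scales are mixed. Whether the slip goes beyond the wording cannot be settled from the article. Severity is minor to moderate: an easily corrected error, which deserves attention because it sits in the definition of the primary outcome.

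**What to change.** Replace the scoring sentence with: percent score = total score / (2 × number of applicable items) × 100, range 0 to 100. State the range explicitly, so that a value above 100 is recognised as an error.

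Then confirm which formula is used in scoring. If any scores were computed with the published one, rescore them from the item data. Because the factor is exactly 2, halving those scores should give the same result and serves as a check.

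The cost is one line of text, a check of the scoring and, at most, a recalculation. Participants, design, assessments and sample size are untouched, and there is no downside.

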#### Secondary outcomes (body structure and function and activity and participation levels)

##### Objective scooter skills

Objective scooter skills will be measured using Kirby et al.’s Wheelchair Skills Test [20]. The test consists of 29 rater administered items that include operating the scooter and indoor and outdoor scooter skills, similar to the subjective version. The ICC for the test-retest reliability of the objective version of the measure among 20 experienced scooter users is 0.90 (95% confidence interval, 0.74–0.95) [26].

##### Satisfaction with participation in selected activities

The WhOM is a participant-specific tool that evaluates satisfaction with participant-identified home and community activities associated with wheeled-mobility provision using an 11-point scale (0 = completely unsatisfied to 10 = completely satisfied) [21]. A mean satisfaction score is calculated by dividing the sum of all satisfaction scores by the number of goals. The WhOM demonstrates promising psychometric properties among community-dwelling, power-mobility users with good 2-week test-retest reliability (ICC = 0.91 for the mean satisfaction score) [27] and moderate correlations with other measures of social participation and device satisfaction [28].

##### Mobility

The Life Space Assessment [29] is a self-report measure of participants’ frequency and independence of mobility in increasingly larger life spaces (e.g., within their (1) home, (2) yard, (3) neighborhood, (4) city or town, and (5) beyond) over the past month. Frequency is measured on a four-point scale: 1 = less than once per week; 2 = 1–3 times per week; 3 = 4–6 times per week; and 4 = daily. Independence is measured on a three-point scale (1 = personal assistance required; 1.5 = assistive device used; 2 = independent). A total composite life-space score, which varies from 0 to 120, can be calculated by multiplying the frequency by the independence by the weighting for each life space (1–5) and adding these together. Among power-mobility users (scooter and power-wheelchair users), the 2-week test-retest reliability is high for the composite score (ICC = 0.87) [30]. Life-space mobility has been found to be significantly higher for those who have had their power-mobility devices for six months or longer [31].

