## Methods

### Study design

To conduct this exploratory, mixed-method, rater-blinded RCT, a two-step wedge design will be used, as illustrated in Fig. 1. With a step-wedge design, participants are randomly assigned to receive the same intervention at different times [22]. For this study, a total of 40 participants, stratified based on whether or not they have previously held an automobile driver’s license, will be randomly assigned to either the immediate intervention group or the delayed intervention group. As illustrated in Fig. 1, the immediate intervention group will receive the intervention after consent and baseline data have been collected, while the delayed group will receive the intervention after a 6-week delay. The primary endpoint of this study is at 6 weeks, so we can compare the effects of the intervention with the group who has yet to receive it.

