### Procedure

The research coordinator and principal investigator will train raters to administer all study measures. This training will include review of manuals, observations of pre-recorded mock interviews and assessments with practice scoring, practice administration with other research staff with feedback provided, and video recording of practice administration for self-reflection.

Upon enrolment, participants will be provided with a unique ID number, and the researcher will obtain written consent prior to baseline testing with all participants. The immediate intervention group will receive SCOOT after their baseline testing once or twice per week over a 6-week period (varying from 9 to 18 hours total), while the delayed intervention group will receive SCOOT 6 weeks after baseline testing. Upon completion of the intervention, all participants will be re-assessed at 6, 12, 26, and 52 weeks after randomization. Participants will also be asked not to participate in any additional training until 12 weeks have elapsed. The intervention will be discontinued upon the participant’s request, or if they are unable to continue with the research due to unforeseen events (e.g., illness).

Measures will be administered in a random order to reduce order effects. All measures, except the Wheelchair Outcome Measure (WhOM), will be collected by a blinded research assistant. The WhOM will be administered by the study therapist as this will inform the intervention. During training sessions, the therapist delivering the intervention will record any adverse effects of the intervention such as falls. As suggested by Little et al. [24], to reduce missing data, we will stress, during the consent process and whenever there is contact between participants and study personnel, the importance of collecting measurement data for the duration of the study, especially for those who discontinue the intervention.

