##### Scooter use and incidents

Participants will be asked to keep a diary of any scooter-related adverse events, including the following: tips or falls from the scooter, injuries to self, accidental contact with others, injuries to others, and damage to property. Participants will be asked to record the number of hours per day that they use their scooters over the course of the study.

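### At 6 weeks the Life Space past-month window lies inside the immediate group's training and outside any training for the delayed group, so session outings can be scored as mobility in one arm only

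*Protocol article*

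**What the plan says.** Four parts of the protocol article bear on this.

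- **Mobility (secondary outcomes).** The Life Space Assessment is self-reported and looks back "over the past month. Frequency is measured on a four-point scale: 1 = less than once per week; 2 = 1–3 times per week". It covers five levels: "within their (1) home, (2) yard, (3) neighborhood, (4) city or town, and (5) beyond". Independence is coded "1 = personal assistance required; 1.5 = assistive device used; 2 = independent", and the composite is built as follows: "A total composite life-space score, which varies from 0 to 120, can be calculated by multiplying the frequency by the independence by the weighting"; the products are then summed over the five levels.
- **Study design.** "The primary endpoint of this study is at 6 weeks, so we can compare the effects of the intervention with the group who has yet". The untrained comparator at that visit is thus the delayed group.
- **Procedure and Experimental intervention.** The immediate arm "will receive SCOOT after their baseline testing once or twice per week over a 6-week period (varying from 9 to 18 hours total"). The delayed group starts 6 weeks after baseline, and everyone is re-assessed at 6, 12, 26 and 52 weeks after randomization. Training is delivered in the participant's own neighborhood, with shops, parks and community centers among the example venues, and "skill training (i.e., on driving, basic and advanced scooter skills) will take place during self-selected, home- or community-based activities".
- **Scooter use and incidents; Analysis.** "Participants will be asked to record the number of hours per day that they use their scooters over the course of the study". Use is listed among the count outcomes for Poisson regression. Effect sizes for the non-count secondary outcomes come from models that control for baseline.

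The article does not say whether trips made as part of a training session count toward the Life Space score or the diary hours.

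**The concern.** The 6-week visit suits the primary outcome, perceived skill capacity, because that reflects the participant's ability at the visit. The Life Space score instead describes what the participant did over the preceding month. In the immediate group that month consists entirely of training weeks, and training here means going out on the scooter to real places near home. The intervention as delivered can therefore be counted as the outcome, in one arm only.

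The Background section makes estimation of intervention effects and their variances part of the feasibility aims, and the results are meant to inform a larger trial. A 6-week Life Space difference that mixes delivered sessions with self-initiated trips does not show how much participants' own mobility changed, and it is an unsafe planning figure if used alone. The same applies to hours of scooter use.

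**Working it through.** **Scale check.** The maximum is the sum over levels of weight × frequency × independence: (1+2+3+4+5) × 4 × 2 = 120. This matches the stated upper limit, so the scoring rule can be used as written.

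**Recall window at each visit.** Take training to run from day 0 to day 42 in the immediate group and from day 42 to day 84 in the delayed group, and a month as 28 to 31 days.

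| Visit | Window | Immediate group | Delayed group |
|---|---|---|---|
| Baseline | before day 0 | no sessions | no sessions |
| Week 6 | day 11–14 (42−31, 42−28) to day 42 | wholly inside training | no sessions |
| Week 12 | day 53–56 (84−31, 84−28) to day 84 | after training | wholly inside training |
| Weeks 26, 52 | later | after training | after training; no untrained arm remains |

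The week-6 window covers 28/42 = 67% to 31/42 = 74% of the immediate group's course. Neither arm has sessions in its baseline window, so adjusting for the baseline score cannot remove an imbalance that arises only at week 6. No visit sets a training-free window in trained participants against an untrained group.

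**Points at neighborhood level (weight 3).** One or two sessions a week are enough by themselves for frequency code 2. The change in score is 3 × independence × change in frequency code, if independence stays the same.

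| Change in frequency code | Independence 1 | 1.5 | 2 |
|---|---|---|---|
| none | 0 | 0 | 0 |
| one category up (1→2 or 2→3) | +3 | +4.5 | +6 |
| not visited → code 2 (0→2) | +6 | +9 | +12 |

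A level not visited is taken as 0, which the stated minimum of 0 implies.

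**If the therapist's presence changes the independence code.** The protocol does not say how a mix of accompanied and unaccompanied trips is coded.

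- Two own trips a week with a device score 3 × 2 × 1.5 = 9. One added session leaves frequency at code 2. If independence is recoded to 1, the score becomes 3 × 2 × 1 = 6, a change of −3.
- Two own trips plus two sessions make four a week (code 3). At independence 1.5 the score is 3 × 3 × 1.5 = 13.5 (+4.5). If recoded to 1 it is 3 × 3 × 1 = 9 (no change).

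**Diary.** Spread over 42 days, training adds 9/42 = 0.21 to 18/42 = 0.43 hours per day in the immediate group and none in the delayed group, if sessions are logged as use and do not replace other use.

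**The case against.** The strongest reply is that overlap in time is not yet bias, and that its direction is not fixed.

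- **Many participants may not change category.** Code 2 spans one to three trips a week. One own trip plus one or two sessions stays there, as do two own trips plus one session. The scale counts all mobility, not only scooter trips, and participants live in the community and are partly recruited through seniors' groups and centers. Home-based sessions add nothing at neighborhood level, and a session built on a self-chosen activity may replace a trip the person would have made anyway.
- **Scores can fall**, as the independence example shows.
- **Town level is not stated.** A reader might infer that sessions also score at city or town level (weight 4). The protocol places training in the participant's neighborhood, so larger figures on that basis are not supported.
- **Excluding sessions has its own risks.** It can over-correct when a session replaces an own trip, and asking about training may prompt participants to reveal their group to the blinded rater.
- **Rater scripts belong in manuals**, and session hours already logged by therapists could be subtracted at analysis.
- **The stakes are limited.** This is one secondary outcome in a 40-person feasibility study, and the primary outcome is untouched.

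All of this narrows the size, and the over-correction risk shapes the remedy. It does not remove the problem: the recall period, visit schedule and training setting are all fixed in the protocol. If a manual already separates training trips, the Life Space part of the point is met. If not, no analysis plan can recover them from a frequency category. The diary is easier, because session lengths are recorded and can be subtracted.

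**Conclusion.** The point holds as one of interpretation and measurement. At week 6 the Life Space window is wholly inside training in one arm and wholly outside it in the other, and no other visit offers a clean contrast with an untrained group. For an individual, the effect at neighborhood level runs from a small loss (−3 in the example), through zero, to +3 to +6 for one category and +6 to +12 from never to weekly. Diary use can be raised by 0.21–0.43 hours per day.

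Two stronger readings are tempting. A reader might infer that the 6-week difference would be positive even if SCOOT changed nothing participants do on their own. The protocol does not support that, because unchanged categories, substituted trips and recoded independence give zero or negative changes. A reader might also divide one participant's gain by an assumed standard deviation and call the result the bias of the comparison. The bias is an average over all participants in the arm. It depends on baseline trip frequency, substitution and coding, none of which the document gives, so it cannot be computed from it.

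Assumptions: the Life Space Assessment is given at week 6, inferred from the re-assessment schedule in the Procedure section because Fig. 1 is not shown; training starts close to randomization; and at least some sessions take place outside home and yard.

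**What to change.** 1. **Life Space Assessment.** At every visit, and with identical wording in both arms, keep the standard score and also record it excluding trips made as part of a scooter training session. Remind participants not to tell the rater which group they are in.
2. **Reporting.** Give the 6-week mobility effect both ways. Do not read the standard score alone as a change in self-initiated mobility, and do not use it alone to plan the larger trial.
3. **Diary.** Mark training hours in a separate column, or subtract the session lengths that therapists already log, when analyzing use. Keep total hours as the exposure for incident rates, since incidents can also occur during sessions.

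**Cost.** A short addition to the rater script and one diary column, slightly more recall effort, and a small departure from standard administration. The training-excluded score may over-correct where a session replaced an own trip, which is why both versions should be reported.
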